## Methods/Design

### Design overview

A prospective, longitudinal, experimental design involving three time points (baseline, post-intervention, and follow-up) and two groups (experimental and control) was developed for this project. Participants will be assigned randomly to either the experimental or control group. The longitudinal design will allow the evaluation of the short- and long-term effects of the intervention. Figure 
1 illustrates the overall design and subject flow for this project. All study procedures and consent forms received approval from both the Université de Montréal (certificate number CERFAS-2012-13-007-D) and Sainte-Justine Mother and Child University Hospital Center (file number 3550) ethics and scientific committees.

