### Participants

Based on prior studies testing cognitive-behavioral interventions in adolescents with cancer, eligible participants are adolescents aged 11 to 18 years with a diagnosis of cancer
[23-25]. In keeping with previous research, there will be no specific selection/exclusion based on type, stage, or trajectory of cancer
[11,26-28]. The intervention will be conducted in French. Therefore, participants are required to speak and understand the language. They must be willing to participate in an 8-week mindfulness meditation program and be available to complete the measures 6 months after the intervention. They must not have a diagnosis of severe mental illness.

Based on prior mindfulness intervention studies with adolescent populations and on usual number of participants in a mindfulness-intervention training group (as indicated by Kabat-Zinn and colleagues
[29] in the MBSR program) a final sample size of 28 participants is targeted
[13,29-33]. Taking into consideration attrition rates from prior research (20-30%), an additional 12 participants will be recruited
[2,34-36]. Thus, a total of 40 participants will be recruited. Participants will be randomly assigned to the experimental or control group, and immediately given a participant ID for confidentiality and anonymization purposes. Twenty adolescents will be completing the mindfulness meditation intervention, which will be taught by two trained therapists (doctoral clinical psychology student and psychiatrist). The intervention will comprise of eight weekly sessions, lasting 90 min each.

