### Randomization

Participants will be assigned to one of two groups according to a computer-generated randomization list (computerized random numbers). As such, participants will be randomly assigned with a 1:1 allocation ratio following permuted block design procedures, using block sizes of four. No stratification criteria will be used. The allocation sequence will be generated by an independent researcher not involved in this project after baseline measures, thus ensuring that therapists and recruiters are kept blind to the allocation of each participant. The allocation sequence will be password protected and only accessible by the independent researcher. The research assistant responsible for the logistics of this project - who is not part of the treatment team - will not be kept blind for allocation and will be responsible for contacting participants randomly assigned to the experimental condition.

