### Wait-list

The use of a wait-list control condition has been compelling in past studies on MBSR and cancer to test for the effectiveness of the intervention without compromising recruitment, while favoring retention of participants who will later benefit from the intervention
[36,37]. Once the follow-up assessment has been completed with the experimental group, wait-list controls will be offered to complete the mindfulness-based program. The data collected on these participants through the second round of intervention will also be analyzed to test the mindfulness-based intervention.

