### Measures

#### Assessment time-points

Measures will be completed by all participants (that is, experimental and control group) at three moments in time: (1) baseline, after the screening interview, consent forms are signed and enrollment is confirmed; (2) immediately post-intervention, at the end of the eighth session; and (3) at 6 months follow-up, when questionnaires will be sent out by mail. At each time period, participants will fill out the questionnaire package, taking approximately 60 min to complete. There will be time allocated at the first and last sessions to complete questionnaires on site. After the third assessment period, once the last questionnaire package has been sent back to the research team, a $10 iTunes gift cards will be mailed to each participant to thank him/her for his/her participation. All measures and corresponding assessment time-points are illustrated in Figure 
2.

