### Planned statistical analyses

Descriptive statistics on participant characteristics will be presented for each group at baseline. Means and standard deviations on primary and secondary outcome variables will be presented for each group at 8 weeks and 6 months.

The cut-point to reject the null hypothesis will be set at 5% (α ≤0.05). Primary hypotheses will first be tested using three mixed analyses of covariance (ANCOVA) with Bonferonni corrections and individual critical alpha levels at 1.67% (α ≤0.0167), that will allow comparison of data at each time-point
[54]. The use of mixed ANCOVAs will help reduce within-group error variance, namely by controlling for baseline differences between participants in each condition and by taking into account possible confounds (for example, age, diagnosis, cancer stage), while providing a higher statistical power in detecting an intervention effect (
[55,56]).These intra-group analyses will serve to evaluate the impact of the mindfulness-based meditation intervention on quality of life, sleep, and mood pre-post intervention, as well as follow-up.

Specifically, changes in quality of life scores (as indicated by the Pediatric Cancer Quality of Life Inventory) between baseline, 8 weeks and 6 months will be tested. Similarly, a change in sleep quality scores (as indicated by the Pittsburgh Sleep Quality Index) and mood scores (as indicated by the Depression and anxiety scales of the Beck Youth Inventories and the PANAS-C) will be tested between baseline, 8 weeks and 6 months. These analyses will also serve to test secondary hypotheses, by allowing inter-group comparisons between the experimental group and the wait-list controls. Specifically, a difference in quality of life scores, sleep quality scores, and mood scores at baseline, 8 weeks, and 6 months will be assessed between groups.

Comparable analyses will be conducted on the data collected from the second experimental group once participants from the wait list condition go through the intervention. All statistical analyses will be conducted using SPSS version 20 (SPSS Inc., Chicago, IL, USA).

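### The treated wait-list group is to serve as a second test of the programme, although by then no untreated arm is left and only an uncontrolled pre-post comparison remains

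*Protocol article*

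**What the plan says.** Design overview describes two groups and no third. Under Randomization, participants are "randomly assigned with a 1:1 allocation ratio following permuted block design procedures, using block sizes of four". Under Wait-list, the crossover is set out: "Once the follow-up assessment has been completed with the experimental group, wait-list controls will be offered to complete the mindfulness-based program". The same section gives the purpose of the later data: "The data collected on these participants through the second round of intervention will also be analyzed to test the mindfulness-based intervention".

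Planned statistical analyses then refers to these participants as a second experimental group: "Comparable analyses will be conducted on the data collected from the second experimental group once participants from the wait list condition" have been through the programme. The analyses they are to be comparable with are three mixed ANCOVAs, each at a critical level of 1.67%. The section calls them intra-group analyses and gives them a second use: "These analyses will also serve to test secondary hypotheses, by allowing inter-group comparisons between the experimental group and the wait-list controls".

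No section describes the second round as uncontrolled, descriptive or exploratory.

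**The concern.** The randomised phase can separate a programme effect from the ordinary course of illness because some participants are untreated over the same months. The second round loses that feature. Repeating the first-round analyses on it either calls for a comparison with nobody to compare with, or leaves a significance test of change over time in one treated group.

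In this population, change over time is to be expected without any intervention. Participants sets no restriction on type, stage or trajectory of cancer, and Discussion expects deterioration and new rounds of treatment. Recovery after treatment would be credited to the programme, and relapse could hide a benefit. The participants are also not the randomised control arm. They are those who remained to the end of a wait of at least 8 weeks plus 6 months and then accepted an offer. At stake is how a result from a group labelled experimental would be read: a favourable change would carry the authority of a test without a control behind it.

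**Working it through.** **The plan's own figures.** The final target is 28 and assumed attrition is 20-30% (Participants). At the upper rate, 28 / (1 - 0.30) = 40, the stated total to recruit. With 1:1 allocation this gives 20 per arm. The per-test level is 0.05 / 3 = 0.0167, as stated. Both reproduce. The article gives no power figure to check.

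**Untreated participants in the second round.** There are two arms. The experimental arm has been treated and followed for 6 months before the offer is made, and the control arm is the one now being treated. Concurrent untreated controls: 0. Assessment time-points lists no further assessment of the first group in parallel.

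**Who is left.** 20 x (1 - 0.20) = 16 and 20 x (1 - 0.30) = 14 controls remain at the end of the first round, before refusals. The article gives no uptake figure. If all accept and 20-30% drop out again (assumption), the range is 14 x 0.70 = 9.8 to 16 x 0.80 = 12.8, or about 10 to 13 analysable.

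**False-positive rate of an uncontrolled pre-post test.** A two-sided paired t-test stands in for the within-group contrast. Sidedness is not stated, so two-sided is assumed. The true programme effect is zero. Scores drift by d standard deviations over the interval, and pre and post scores correlate at r. Both d and r are assumptions.

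- Noncentrality: d x √n / √(2(1 - r)).
- Critical value at 0.05/3 with n = 14 (13 degrees of freedom): 2.746.
- Example, d = 0.5 and r = 0.5: 0.5 x 3.742 / 1 = 1.871, rejection probability 23%.
- Example, d = 0.5 and r = 0.7: 0.5 x 3.742 / 0.775 = 2.415, rejection probability 40%.

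| Natural drift | n = 14, r = 0.5 to 0.7 | n = 10, r = 0.5 to 0.7 |
|---|---|---|
| 0 | 1.67% | 1.67% |
| 0.2 SD | 4.3% to 6.4% | 3.4% to 4.6% |
| 0.3 SD | 8.3% to 13.6% | 5.7% to 8.8% |
| 0.5 SD | 23% to 40% | 15% to 25% |

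The nominal level holds only with no drift, and the second round has no arm from which drift could be estimated. Covariates such as age, diagnosis or stage do not solve this: they explain differences between participants, and in a single treated group they cannot separate drift from programme effect.

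**The case against.** The strongest reply is that comparable does not mean identical. The sentence concerns one group's data, and the article itself calls its main analyses intra-group. On that reading only the within-group part is repeated, which can be done. This is fair: the article does not say that a between-group contrast will be run in the second round. It does not rescue the plan, because the within-group part is exactly the uncontrolled test examined above, and its stated purpose is still to test the intervention.

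A second reply is that this is a pilot. Pilot study endpoints speaks of indications of potential benefit, and the randomised comparison is untouched. This lowers the stakes and stands to that extent. But the second round inherits significance tests, and nothing marks its results as weaker evidence than the first round's. It is also true that the randomised phase gives pre-post change a leading role. That is a separate matter, since a control arm exists there.

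A reader might go further in four ways that the article does not support.

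- *That the enrolment baseline is the second-round pre value.* No section says so. Assessment time-points allots questionnaire time at the first session, and controls also have a 6-month score.
- *That more than a year necessarily separates the pre score from the first treated session.* That needs the enrolment baseline as pre value, the earliest enrolled control and a single group of 20. The screening section also allows a start with 10.
- *That the second round will be pooled with the randomised comparison or presented as a replication.* Neither is planned.
- *That the controls' first interval is a clean untreated 8 weeks.* They are measured at enrolment, and the screening section allows a delay of weeks to months before the programme starts.

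Finally, selection is inferred from the offer and the expected attrition. The article does not report it.

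**Conclusion.** The concern holds in a limited form. The article gives the second round the role of a test when no untreated group exists. What can be run is a pre-post comparison in at most 14 to 16 of the 20 controls at the stated attrition, fewer if some decline. With no programme effect and a drift of 0.2 to 0.5 SD, it would reject in about 4% to 40% of cases at n = 14, against a nominal 1.67%. The absence of controls and the head count follow from the document. The rejection rates rest on the assumed drift, correlation and two-sided paired test, and they show the scale of the problem without predicting it. The randomised comparison is unaffected. The wording on the second round should be changed, because as written it would credit natural change to the programme.

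**What to change.** In Wait-list and in Planned statistical analyses, replace the stated purpose of testing the intervention, and the reference to comparable analyses, with a supportive, non-randomised analysis kept separate from the randomised comparison. Specify the following.

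1. The pre value is taken at or just before second-round entry: the 6-month score or the first-session questionnaire, with one named in advance.
2. The second-round change is reported with a confidence interval, beside the same participants' change over their untreated waiting period. Show the actual interval lengths, because the time from enrolment to the post-intervention assessment can exceed 8 weeks.
3. The text notes that this within-person reference remains confounded with time, including time since diagnosis or treatment.
4. The numbers of controls offered the programme, accepting it and completing it are reported.

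The cost is small. The waiting-period assessments are already planned for all participants, and second-round data are already to be collected. A first-session questionnaire, if chosen and not already intended for this group, adds one administration of about 60 minutes; using the 6-month score adds none. The price is a more modest claim from the second round.

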### Statistical power

Effect sizes will first be calculated using partial eta squared (partial η^2^) in order to evaluate the pre-post effect of the intervention. Cohen’s d will also be calculated in order to evaluate the effect of the intervention between groups. Based on the previous literature on MBSR and oncology, small effect sizes are usually found
[36]. Given the pilot-testing nature of this study, it may be that we will not detect large group differences. In this perspective, clinical significance and cues of intervention success will be evaluated based on individual courses and established cut-points for each primary outcome variable. Participant journals may also be taken into consideration for qualitative information regarding the intervention.

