### Pilot study endpoints

Based on previous research, the following criteria will be evaluated in order to assess the feasibility of a subsequent, larger trial
[57]:

1. Recruitment and retention: Recruitment effectiveness will be closely monitored and documented, along with recruitment strategies. Ineffective strategies will be eliminated in subsequent trials. Retention and attrition rates will also be taken into consideration in developing further trials, especially in regards to future estimates of sample sizes and inclusion/exclusion criteria, if relevant.

2. Feasibility and design assessment: Notes will be taken regarding design flow and overall progress of this project, namely the time frame required to complete each step planned in this design and the overall study.

3. Intervention and measure assessment: Participants will be asked to provide feedback to the therapists regarding their appreciation of the mindfulness intervention. They will also be asked if they would recommend this intervention to peers with cancer. Measure assessment and acceptability will be evaluated according to rates of completion of each questionnaire after the last assessment point. Thus, measures with low completion rates or poor understandability will be reconsidered for subsequent, larger trials.

4. Outcome assessment: Statistical analyses will provide indications of potential beneficial effects of the mindfulness intervention, namely with effect sizes as indicators of the magnitude of observed improvements on mood, sleep, and quality of life. These results could help in evaluating the relevance of including these variables in further trials.

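### Signs of success are to be read from individual courses and cut-points with no stated wait-list comparison, and pre-post partial eta squared is treated as an intervention effect; both can look favourable with no effect

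*Protocol article*

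**What the plan says.** Under Statistical power, the Protocol article plans partial eta squared "in order to evaluate the pre-post effect of the intervention" and, in the next sentence, Cohen's d for the effect between groups. Both are planned whatever the group comparison shows. The section then notes that effects in this field are usually small and that a pilot may not detect large group differences. From that viewpoint, "clinical significance and cues of intervention success will be evaluated based on individual courses and established cut-points for each primary outcome variable". It gives no cut-point values, no definition of a responder, and no statement that the wait-list arm is assessed in the same way.

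Other sections bear on the reading:

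- Primary aim states the expected improvement as a change from before to after the intervention in the experimental group.
- Planned statistical analyses describes the primary tests as within-group and gives the between-group comparison to secondary hypotheses. It also plans adjustment for baseline differences, and means and SDs for each group.
- Assessment time-points has both arms complete all measures at baseline, post-intervention and 6 months.
- Pilot study endpoints, item 4, takes "effect sizes as indicators of the magnitude of observed improvements on mood, sleep, and quality of life" and says that the results could help in judging whether these variables belong in further trials.

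**The concern.** An individual who moves from the unfavourable to the favourable side of a cut-point may have responded to the intervention. The same move can come from measurement error, regression to the mean, the end of a treatment round or ordinary recovery. Only the wait-list arm separates these. Pre-post partial eta squared has the same weakness. It also carries no sign and is above zero on average when nothing changes. In a trial open to any cancer stage or trajectory, change over 8 weeks and 6 months without the intervention is plausible.

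The route matters because the trial is likely to take it. With a small expected effect and 28 completers, the between-group test will seldom be significant, so the reader's impression of promise will rest largely on individual courses, cut-points and effect sizes. At stake are the encouragement that the pilot gives to a larger trial and, through item 4 of Pilot study endpoints, the choice of outcomes for it.

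**Working it through.** **Inputs from the Protocol article.** Completers: "a final sample size of 28 participants is targeted", so 14 per arm at 1:1. Test level: "individual critical alpha levels at 1.67% (α ≤0.0167". Reliabilities (Primary outcome measures): above 0.73 for the Beck scales, so 0.73 is a lower bound, and 0.85 test-retest for the sleep index.

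**Assumed, because the article gives no figure.** Two-sided tests; d = 0.2 for a small effect; cut-point at +1 SD, with +0.5 to +1.5 SD as the range; normal scores; the stated reliabilities used as pre-post correlations.

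**1. The plan's own figures.** 28/(1 − 0.30) = 40, the recruitment total. 0.05/3 = 0.0167. Both reproduce.

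**2. How likely the between-group test is to decide matters.** Unadjusted, with 14 per arm, power for d = 0.2 is 3% at 0.0167 and 8% at 0.05. For d = 0.5 it is 13% and 25%. The smallest observed d that is significant at 0.0167 is t(0.99165; 26 df) × √(2/14) = 0.97. Baseline adjustment helps only modestly: at a pre-post correlation of 0.6, power for d = 0.2 at 0.0167 is 4%.

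**3. Cut-points with no true change.** For bivariate normal scores with correlation r and cut-point c, P(below later | above at baseline) = 1 − P(both above)/P(above).

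| Cut-point | r = 0.73 | r = 0.85 |
|---|---|---|
| +0.5 SD | 34% | 25% |
| +1 SD | 45% | 33% |
| +1.5 SD | 55% | 42% |

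At +1 SD, 15.9% of 14, or 2.2 participants, start above the cut-point. Expected favourable crossers are 2.2 × 0.447 = 1.0 and 2.2 × 0.333 = 0.7. By symmetry the same number is expected to cross the other way. With wider assumptions (r from 0.5 to 0.85, 20-50% beyond the cut-point at baseline), 18-56% of those beyond it fall back. The probability that at least 1 of 14 crosses favourably on one scale is then 0.59-0.92.

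**4. Partial eta squared with no true change.** Its null mean is df1/(df1 + df2).

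- One-arm pre-post model, 14 completers: 1/(1 + 13) = 0.071; it exceeds 0.06 in 38% of trials.
- Two-arm model, 28 completers, before covariates: 1/(1 + 26) = 0.037, and the same for 2/(2 + 52); it exceeds 0.06 in 20-21%.

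The article calls these analyses within-group but specifies mixed ANCOVAs on two groups, so either model could be meant.

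**5. Change shared by both arms.** In 20,000 simulated trials per setting, with 14 per arm, correlation 0.5-0.7 and zero intervention effect, both arms improve by 0.3-0.5 SD. Mean one-arm pre-post partial eta squared is then 0.14-0.32. The within-arm test at 0.0167 favours improvement in 8-40% of trials. The between-arm comparison of the same data rejects in about 1.7%, its nominal level.

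**6. Precision of the between-arm effect size.** SE(d) is about √(2/14) = 0.378 unadjusted. Baseline adjustment multiplies it by √(1 − r²).

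| Analysis | SE | 95% half-width | Wrong sign if d = 0.2 |
|---|---|---|---|
| Unadjusted | 0.378 | 0.74 | 30% |
| Adjusted, r = 0.73 | 0.258 | 0.51 | 22% |
| Adjusted, r = 0.85 | 0.199 | 0.39 | 16% |

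**The case against.** The article does not exclude the controls. They are measured at every time point, group means and SDs are to be reported, and a between-group Cohen's d is planned in the same paragraph. A condensed article may leave responder definitions and tabulation by arm to a fuller document. The wording is modest: it speaks of cues in a pilot, sets no threshold for success, and individual courses would show worsening as well as improvement. The number of chance crossers is small and balances out.

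Most of this stands, and it rules out three stronger readings that a reader might infer:

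- That partial eta squared is a fallback replacing the group comparison. It is calculated in any case.
- That success will be read with the control arm left out. The text is silent on the comparison, and silence is not exclusion.
- That outcomes will be kept or dropped on observed effect sizes. Item 4 says only that results could help. Item 3 looks to completion and understandability, and item 1 to retention.

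What remains is not a matter of omitted detail. The article does state how signs of success will be judged and does call a pre-post quantity an effect of the intervention. Its aims and primary analyses have the same within-group focus. Followed as written, the text lets change unrelated to the intervention be credited to it. Pilot status does not remove this, since guiding the next trial is the pilot's purpose.

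**Conclusion.** The point holds in a limited form. The plan judges signs of success from individual courses and cut-points without stating a wait-list comparison, and it attaches the intervention's name to a pre-post effect size. These can look favourable with no effect; the documents do not support saying that they will.

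Regression to the mean alone has a modest effect: about 1 favourable crosser in 14 per scale at +1 SD, with an equal number expected the other way. It misleads mainly if only favourable crossings are counted. Null partial eta squared of 0.037-0.071 is also modest. Shared recovery is the larger risk, but its size here is unknown; the 0.3-0.5 SD used above is an assumption. The cut-point position and the use of reliabilities as pre-post correlations are assumptions too. Because 0.73 is a lower bound, 45% is the upper end for the Beck scales at +1 SD if the pre-post correlation is at least the stated reliability. Baseline adjustment, which the plan intends, narrows the interval for the effect size, but a small effect would still have the wrong sign in roughly one trial in five or six.

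**What to change.** In Statistical power:

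- Apply each cut-point in both arms, show crossings in both directions, and report the between-arm difference in proportions with a 95% interval.
- Make the baseline-adjusted between-arm standardised difference, with its 95% interval, the measure of intervention effect.
- Label pre-post partial eta squared and individual courses as descriptive.

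In Pilot study endpoints, item 4:

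- Use the same between-arm measure, and say that effect sizes are read with their intervals (half-width about 0.74 unadjusted, or 0.4-0.5 if the pre-post correlation is 0.73-0.85).
- State that no outcome is chosen for the larger trial on its point estimate alone.

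No new data are needed, because both arms already complete every measure. The cost is some rewording, small extra tables, and results that may look less favourable.
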